### Participants

Overall, 700 participants are being recruited, with approximately half of the consecutive qualifying cases being randomised to MST alone, and the other half to MAU. The unit of randomisation is the individual participant.

### Sample size and power calculation

It is estimated that each site will have at least 140 families per year referred for treatment. On the basis of past experience, data from a meta-analysis of previous trials of MST (including major effectiveness trials from the US) that was carried out in the course of preparation of the NICE guidelines [2], and assumptions outlined below, the investigators assume that about 30% of referred families will meet the criteria and agree to randomisation; this implies that each site will be able to recruit and treat 70 to 80 families during a recruitment window of 18 months. Therefore, investigators expect to be able to recruit and assess 700 participants (350 in each arm). Figure 1 shows the expected flow of participants from recruitment through to the end of the study.

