### Study setting

The study involves each of the 10 MST pilot sites in the UK. Recruitment at each site will take place for 18 months, commencing about 12 months after the inauguration of the programme at each site (sites have begun the programme at different time points), to ensure the embedding of MST at each site before randomisation begins, as described above. At each site, a team of four MST therapists is guided by a supervisor - a doctoral-level (or master’s-level with significant clinical and supervisory experience) therapist with sound knowledge of the theories underpinning MST and their application, and experience in providing clinical supervision. The MST supervisor conducts weekly group supervision, and one-to-one supervision if needed, of the MST therapists at a site to ensure they are adhering to MST principles in their practice. The supervisor is also involved in the selection of young people referred to the service as suitable for MST (see Recruitment and baseline procedures below).

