**Figure 1 F1:**
[figure not shown]
**CONSORT flow diagram of progress through the phases of recruitment and treatment in the START trial of multisystemic therapy.** CAMHS, child and adolescent mental health services; MAU, management as usual; MST, multisystemic therapy.

Assuming that 30% of the MAU arm will have out-of-home placements, this sample size will give 86% power to detect a 10% difference in out-of-home placements (a reduction from 30% to 20%). To take account of within-therapist correlation of outcomes in the MST arm, an intraclass correlation of 0.02 and a total of 30 therapists has been assumed, giving design effects of 1.22 in the MST arm and 1.0 in the MAU arm, and thus reducing the power to 83%.

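### The stated referral and uptake figures yield about 63 families per site (630 in all), not the 70 to 80 per site and 700 drawn from them

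*Protocol article*

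**What the plan says.** All of this is in the Protocol article, Methods/Design.

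- **Referrals** (Sample size and power calculation): "It is estimated that each site will have at least 140 families per year referred for treatment".
- **Uptake** (same paragraph): "about 30% of referred families will meet the criteria and agree to randomisation".
- **Conclusion drawn** (same sentence): "this implies that each site will be able to recruit and treat 70 to 80 families during a recruitment window of 18 months". The next sentence infers from this that 700 participants, 350 per arm, can be recruited and assessed.
- **Window and sites** (Study setting): "Recruitment at each site will take place for 18 months", and "The study involves each of the 10 MST pilot sites in the UK".
- **Power** (same sample-size section, after the Figure 1 caption): 86% for a fall in out-of-home placement from 30% to 20% at this sample size. An intraclass correlation of 0.02 and 30 therapists are then assumed, "giving design effects of 1.22 in the MST arm and 1.0 in the MAU arm, and thus reducing the power to 83" per cent.
- **Significance level** (Statistical analysis plan, Secondary outcomes): two-sided 0.05 for the single primary outcome.

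**The concern.** The per-site yield is presented as a consequence of the referral rate, the uptake and the window, and the total of 700 is presented as a consequence of the per-site yield. A reader who multiplies the three inputs does not get a number in the stated range. The number 700 carries the power statement, and the Discussion relies on the trial being large enough to inform policy. If the published inputs are the real planning assumptions, the trial should expect fewer participants than the power statement uses. If they are not, the article does not show the assumptions on which 700 rests.

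**Working it through.** **1. Accrual from the stated inputs**

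Yield per site = referrals per year x years x uptake
= 140 x 1.5 x 0.30 = 210 x 0.30 = **63**.

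Over 10 sites: 63 x 10 = **630**, or 315 per arm at 1:1.

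Shortfall against 700: 70/700 = 10%.

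**2. What the stated range would need**

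| Target per site | Uptake needed at 140 referrals a year | Referrals a year needed at 30% uptake |
|---|---|---|
| 70 | 70/210 = 33.3% | 70/(1.5 x 0.30) = 155.6 |
| 80 | 80/210 = 38.1% | 80/(1.5 x 0.30) = 177.8 |

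With both rates left as stated, 70 per site needs a 20-month window: 140 x 20/12 x 0.30 = 70.

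**3. Reproducing the article's power at 700**

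Two-proportion normal approximation with pooled variance under the null, two-sided 5%:

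power = Phi[(0.10 - 1.96 x SE0)/SE1], where SE0 = sqrt[p(1-p)(1/n1 + 1/n2)], SE1 = sqrt[0.30 x 0.70/n1 + 0.20 x 0.80/n2], and p is the average proportion weighted by n1 (MAU) and n2 (MST).

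- *Unclustered, 350 per arm.* p = 0.25, SE0 = 0.03273, SE1 = 0.03251. Power = Phi(1.102) = **86.5%** (stated: 86%).
- *Clustered.* The MST arm is reduced to 350/1.22 = 286.9 and MAU stays at 350. SE0 = 0.03471, SE1 = 0.03403. Power = Phi(0.940) = **82.6%** (stated: 83%). With unpooled variance it is 83.6%.
- *Design effect.* 1 + (350/30 - 1) x 0.02 = 1.213; the stated 1.22 corresponds to 12 families per therapist. With 1.213 the power is 82.7%, so the difference is immaterial.

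Both stated power figures reproduce at 700.

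**4. The same calculation at 630**

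- *Unclustered, 315 per arm.* SE0 = 0.03450, SE1 = 0.03427. Power = Phi(0.945) = **82.8%**.
- *Clustered, 30 therapists.* Design effect = 1 + (315/30 - 1) x 0.02 = 1 + 9.5 x 0.02 = 1.19. Effective MST size = 315/1.19 = 264.7. SE0 = 0.03631, SE1 = 0.03565. Power = Phi(0.809) = **79.1%**.
- *Sensitivity to method.* Unpooled variance gives 80.1%. Keeping the design effect at 1.22 gives 78.5% pooled and 79.6% unpooled. A continuity correction would give 75.5% to 76.2%, but at 350 per arm it gives about 80% clustered, so it is not the method behind the stated 83%.

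**The case against.** The strongest reply is that the inputs are not exact. The article gives 140 as a minimum and 30% as approximate, so 63 is the yield at the stated values and not a ceiling. Only 70 per site is needed for 700, and 33% uptake might loosely be rounded to 30%. This stands in part: the bottom of the range is within reach if either input runs somewhat higher. It does not rescue the sentence, which claims a deduction from these figures. The top of the range needs 38% uptake or about 178 referrals a year, and no such figure is given. The section does point to assumptions set out further on, but those in the text concern the event rate, the intraclass correlation and the number of therapists, not accrual. Figure 1, on expected participant flow, was not legible in the copy reviewed, so it could not be checked for other counts.

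The second reply is that the power figures are tied to 700 and are right for 700. That stands in full. A reader might infer that the article's 83% is an error and that the true power is 79%. The documents do not support that: 79% applies only if recruitment stops at about 630, and 700 is stated as the recruitment number elsewhere in the article (Abstract, Participants, Discussion).

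Two further inferences also fail. Four therapists at each of 10 sites makes 40 rather than the assumed 30, but assuming 30 gives the larger design effect and so the lower power; it does not overstate power. Using all 350 per arm is consistent with the article's expectation of very little missing primary-outcome data.

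**Conclusion.** The accrual statement is wrong as written. Its own inputs give about 63 families per site and 630 in total, 10% short of 700 and below the whole of the 70 to 80 range. The power statement is correct for the sample size it names. Should accrual follow the stated inputs, power would be about 83% unclustered and about 79% to 80% clustered, a loss of roughly 4 points that leaves the trial near 80%. This rests on taking 140 and 30% at their stated values, 18 months at each of 10 sites, 30% against 20% placement, an intraclass correlation of 0.02, 30 therapists in the MST arm only, and a two-sided 5% test.

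It does not follow that the trial will finish 10% short, because the referral rate is a minimum and the uptake is approximate. No endpoint, allocation or analysis is affected. The point merits correction but is not a critical fault.

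**What to change.** Choose one of two restatements in Sample size and power calculation.

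1. **Keep 700 and give the inputs that deliver it.** Any one is enough: about 33% uptake, about 156 referrals per site per year, or a 20-month window per site. Correct the 70 to 80 range to match; each of these gives about 70. If the window is changed, the 18 months in Study setting and Trial status must change with it. This option preserves the stated target and the 86% and 83% figures.
2. **Keep the inputs and restate the yield** as about 63 per site and 630 in total, with power of about 83% unclustered and about 79% to 80% clustered (design effect 1.19).

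The cost is a change of wording. The only downside is a slightly less favourable stated figure: a more demanding accrual assumption under the first option, or lower power under the second.

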**Figure 1 F1:**
[figure not shown]
**CONSORT flow diagram of progress through the phases of recruitment and treatment in the START trial of multisystemic therapy.** CAMHS, child and adolescent mental health services; MAU, management as usual; MST, multisystemic therapy.

Assuming that 30% of the MAU arm will have out-of-home placements, this sample size will give 86% power to detect a 10% difference in out-of-home placements (a reduction from 30% to 20%). To take account of within-therapist correlation of outcomes in the MST arm, an intraclass correlation of 0.02 and a total of 30 therapists has been assumed, giving design effects of 1.22 in the MST arm and 1.0 in the MAU arm, and thus reducing the power to 83%.

### Eligibility criteria

#### Inclusion criteria

The study design aims to increase generalisability of the findings beyond the group of adolescents under study by using the minimum number of entry criteria. The task of establishing an adolescent target population based on the status of ‘being on the edge of care’ is challenging as, in most contexts, this term covers a heterogeneous group. At the same time, it was recognised that the four referral routes used in the study (YOTs, social care, CAMHS or education services) often identify young people and families with very similar needs when they have reached a particular crisis point. The nature of the crisis may be associated with the specific service (for example, YOTs are triggered by convictions, education services by repeated school exclusions) but the underlying causes in terms of family disorganisation, conflict and stressors, combined with antisocial behaviour by the young person, are similar, and the outcomes in terms of risk of out-of-home placement are common to them.

All participants, regardless of referral source, must meet the following general inclusion criteria:

● Young person aged 11 to 17 years;

● Sufficient family involvement for MST to be applied;

● No existing agency involvement that would interfere with MST (for example, the family is already engaged with a therapist);

● Displaying antisocial behaviour manifesting as at least one of the following criteria indicating suitability for MST:

o Persistent (weekly) and enduring (6 months or longer) violent and aggressive interpersonal behaviour;

o A significant risk of harm to self or to others (for example, self-harming, substance misuse, sexual exploitation, absconding);

o At least one conviction and three warnings, reprimands or convictions in the past 18 months;

o Current diagnosis of an externalising disorder and a record of unsuccessful outpatient treatment;

o Permanent school exclusion.

In addition, participants must meet at least three of the following criteria, which are indicative of risk status and serve as generic indicators of risk sufficient to warrant referral to services:

● Excluded from school or at significant risk of exclusion;

● High levels of non-attendance at school;

● A history of offending, or at significant risk of offending;

● Previous episodes on the Child Protection Register;

● Previous episodes of being ‘looked after’, that is, placed outside of the home (whether via incarceration, psychiatric hospitalisation, residential schooling or assignment to residential local authority care);

● Previous referral to a Family Group Conference (usually a meeting between the family members and sometimes also friends or neighbours, the young person and his/her supporter or advocate if requested, and professionals from the health, education or social services to discuss, plan and make decisions regarding a child at risk to prevent the young person from becoming looked after)

● History of siblings being looked after and taken into local authority care.

Guidelines were developed for inclusion depending on the nature of the referral. The specific inclusion criteria for the four agencies and referral paths are briefly summarised in Table 1.

**Table 1 T1:** Inclusion criteria by referral source in the START trial of multisystemic therapy

**Referral source**	**Inclusion criteria specific to the source**^ **a** ^
Children’s services	• Designated as ‘child in need’ where this is associated with antisocial behaviour on the part of the adolescent
	• Exhibiting extremely challenging behaviour by either persistent (weekly) *and* enduring (6 months or longer) violent and aggressive interpersonal behaviour *and*/*or* a significant risk of harm to self or to others (for example, self-harming, substance misuse, sexual exploitation, absconding)
Youth offending teams	• At least one conviction within the past 12 months, or referral via a supervision order with multisystemic therapy as a specified activity
	• A warning, reprimand and/or conviction on at least three occasions in the past 18 months
Child and adolescent mental health services	• Current diagnosis of conduct disorder, substance misuse, major depression or anxiety
	• History of at least one unsuccessful outpatient intervention
	• *Either* history of school exclusion *or* assessment as ‘child in need’
Educational services	• Currently permanently excluded from school
	• History of having been excluded from at least one other school for aggressive conduct

^a^All participants must also meet the general inclusion criteria described in the text.

#### Exclusion criteria

The exclusion criteria applied were:

● History or current diagnosis of psychosis;

● Generalised learning problems (clinical diagnosis) as indicated by intelligence quotient (IQ) below 65;

● Identified serious risk of injury or harm to a therapist or researcher;

● Presenting issues for which MST has not been empirically validated, in particular, substance abuse in the absence of criminal conduct or sex offending as the sole presenting issue.

### Recruitment and baseline procedures

The recruitment process is fundamental to the success of this large, multisite research trial. In addition to criteria that apply to recruitment for any trial (for example, the clear application of eligibility criteria, a standard procedure for obtaining informed consent), recruitment for this trial must be especially sensitive to the community context and be based on effective partnerships with referral agencies and strong relationships with the young people and their families. Consequently, the trial team has developed strong collaborative relationships with the MST team at each site to achieve the high levels of accrual necessary to ensure sample comparability and reasonable generalisability.

The authors developed a multiple gating procedure for recruitment based partly on the experience of the MST trial conducted at the Brandon Centre [44]. Using this procedure, decisions about eligibility for the trial have been made at three points: by the multi-agency panel; through discussions between the MST supervisor and trial coordinator on the basis of information gathered from the referral form; and through discussions between the MST supervisor and trial coordinator following gathering of initial information by the clinical and research teams after an introductory home visit to explain the rationale for the research trial and answer any questions about the clinical services potentially available to the family. Experience suggests that each of these screens tends to reveal different criteria for ineligibility, and their use in combination minimises the (considerable) effort of recruitment. For example, the multi-agency panel review tends to identify referrals for issues for which MST has not been empirically validated (for example, sex offending as the sole presenting issue), whereas discussions between the MST team and family or referral source most commonly identify a risk of possible injury to a worker or agency involvement precluding inclusion in the trial.

Finally, the research assessor’s (RA) assessment is necessary to confirm the young person’s IQ and psychiatric diagnosis.

#### Screen 1

Multi-agency panels have been put in place at each of the 10 sites, taking referrals from YOTs, CAMHS, social care and education services. These panels identify new cases that meet the eligibility criteria for MST. In addition, the MST team at each site directly takes referrals, as they have become established and connected with other services and referral sources in each of their localities. The decisions made by the multi-agency panels and the MST team constitute the first screen. During the period between establishment of the teams and the start of the trial, each MST team gained experience in screening referrals and educating potential referrers as to what constitutes an appropriate referral to the trial. A standard referral form for each locality is used in liaison with the research team, including specific information pertaining to inclusion and exclusion criteria. This forms the first screen to the trial, focusing on establishing the severity and chronicity of antisocial behaviour.

#### Screen 2

Following acceptance of the referral by the multi-agency panel, a standard initial letter from the clinical team, in the first language of the family, is sent to the parents and separately to the young person if aged 16 or over, informing them about the trial. Recruitment begins with this letter, which is sent to all those identified by a panel and/or MST team to be probably suitable for MST. The letter invites participation, and informs the family and the young person that someone from the MST team (preferably the MST supervisor) will contact them unless they do not wish to participate in the trial. The letter includes material in age-appropriate and culturally appropriate language in the form of a leaflet for both the parents and the young person explaining the trial and what involvement in the trial would mean at that particular site. These information sheets have been constructed and designed with input from young people and their parents or carers who have used MST at the same site to make them as useful and accessible as possible.

After 3 to 7 days the family is visited by a member of the MST team to explain what participation might involve and to arrange an appointment at the family home that will include the MST supervisor or therapist, the RA, the young person and his or her primary carer(s). The discussions at this meeting include the identification of an acceptable and credible MAU path (the best available alternative treatment at that locality; see below) should the young person not be randomised to receive MST.

At this meeting, which constitutes the second stage of the multiple screening procedure, the MST therapist identifies possible exclusion criteria, such as a risk of injury or harm to a worker, agency involvement incompatible with participation in the trial, or severe substance dependency. Consent forms are not signed at this appointment because experience has shown that actual take-up of treatment increases dramatically and early drop-outs are reduced if the family feels they have been given adequate time to consider participation.

#### Screen 3 and consent

Unless the family expresses a decision not to participate at the time of the visit or within 3 to 7 days after the visit, a telephone contact is made by the RA, offering a research assessment. At this stage the consent form is reviewed. Consent forms signed by both the young person and carer(s) include permission to access the police and correctional databases, remaining in effect for 3 years. For families who sign the consent forms, the RA administers pre-randomisation questionnaires and measures are completed during this contact (that is, before group assignment). The final evaluation for eligibility (the third screen) is made at this second visit.

When all the instruments have been completed and eligibility for the trial confirmed, the RA telephones the trial centre to inform the centre of the family’s randomisation details. The randomisation is performed and details communicated to the referrer and family within 24 hours.

#### Randomisation and procedures to minimise bias

After consent has been obtained and the baseline assessment has been carried out, a trial identification is assigned. Eligible consenting participants are randomised to MST or MAU on a 1:1 basis by the Trials Unit at University College London using a secure telephone randomisation service that ensures allocation concealment. A computer-generated adaptive minimisation algorithm that incorporates a random element is used with the following stratification factors: treatment centre, gender, age (11 to 14, 15 to 17) and age at onset of conduct problems (2 to 11, 11+). These strata were selected because previous research has shown that a younger age of onset is associated with poorer prognosis; there is insufficient evidence concerning gender mix, particularly in the older age groups, to ensure that simple randomisation would generate comparable groups. Treatment centre is included in the minimisation stratification to control for differences between centres.

To minimise bias that could arise from knowledge of treatment allocation, the following strategies are employed: RAs are blind to treatment allocation; the RA and therapist do not communicate directly (if at all) with each other; qualitative interviews, conducted with a subsample of the families by doctoral students trained and supervised by experienced qualitative researchers, are audiotaped and a random sample re-rated by independent raters. The qualitative interviewers are separate from the MST service providers.

### Planned interventions

#### Multisystemic therapy

There are a number of factors that contribute to the unique nature of MST: it addresses the multidetermined nature of severe conduct problems; it sees the caregiver as key to effective behaviour change; it uses the adolescent’s home as the primary site of the intervention; it integrates several evidence-based intervention techniques; it uses a single therapist to deliver multiple modalities of intervention within a singular conceptual framework; and there is rigorous monitoring of adherence to the model, including the use of comprehensive quality assurance and on-going quality improvement system for maintaining standards.

MST is a family- and community-based intervention that uses intense contact with a family to understand and address the drivers of a young person’s antisocial behaviour. It targets drivers related to the young person’s individual adjustment, family relationships, school functioning and peer group affiliations. A focus on the caregiver and family is key to the intervention. MST interventions are individualised and highly flexible but are documented in treatment manuals [61]. The package is designed to work with hard-to-reach families in the community and provides a duty cover system 24 hours a day, 7 days a week to ensure that families receive support from the MST team at the times when crises are occurring. Although the package comprises a number of evidence-based interventions, it is designed to be delivered by one highly trained professional, typically a mental health professional with graduate training in one of a variety of disciplines (for example, clinical psychology, social work) with a caseload of four to six families. The MST therapist is a full-time generalist who directly provides most of the mental health interventions and directs access to services, coordinating these to monitor quality control. The therapist is available to the family 24 hours a day, 7 days a week but input is adjusted according to need. Treatment fidelity is ensured by weekly group supervision meetings between therapists and the MST supervisor; these meetings may also include a medical consultant. Treatment generally lasts 3 to 5 months. Sessions are held in the family’s home and in community locations [61]. Especially in the beginning, the therapist may be in the home three times a week and may speak to the young person’s parent or principal carer on days when no visit has been arranged. The MST therapist also spends time at the young person’s school as needed and meets with the young person’s peer group and extended family. A key early part of the process is to engage the family, a significant challenge in some cases.

Despite incorporating a range of modalities, MST is more than just an amalgamation of techniques and approaches, and a focus on the inter-relationship between social, education and healthcare systems is retained. The overarching goals of MST are to give parents the skills and resources needed to address the inevitable difficulties of raising adolescents, and to empower adolescents to cope with familial and extrafamilial problems. Assessment and treatment explore the adolescent’s role in various systems and consider the inter-relationship between these systems. Specific attention is given to strengthening the various systems, and an attempt is made to promote appropriate and responsible behaviour among all family members. MST focuses on current behaviours as opposed to influences from the young person’s past. It seeks to identify, reduce and, if possible, remove behaviours that are of concern to the referring service and the young person’s parent or principal carer. The implementation of MST draws on family members, in contrast to many interventions that define the young person as the ‘identified client’. In addition, collaboration with community agencies is a crucial part of MST. For instance, establishing (or in most cases re-establishing) engagement between the young person, the parent(s) and the school is a critical part of the treatment, and the MST therapist may be in regular contact with teachers. The MST therapist also works in close partnership with the social worker from the YOT or social services, who may have statutory responsibilities for the young person. When considered necessary, the young person is referred to a general practitioner or other medical professional who can assess the young person and prescribe medication.

As mentioned above, the MST teams are centrally funded by the Department of Health and had already been operational for approximately 12 to 18 months prior to their participation in the START trial. These factors benefit the RCT in several respects. First, at the start of the trial the clinical teams had already developed relationships with key stakeholders and referrers in their local communities, and multi-agency panels had been in operation to facilitate recruitment. Second, the clinical teams had already had the opportunity to liaise with potential sources of referrals regarding the appropriateness of referrals, and thus to ensure that referral of inappropriate cases is minimised. Third, as the funding of the MST teams is tied to participation in the research trial, the collaboration between the MST clinical teams and the research team to achieve common goals (for example, recruitment numbers, implementation of randomisation, completion of the research protocol) is maximised. Finally, by the start of the trial, the therapists and supervisors would have been able to develop experience implementing MST; research suggests that mature MST teams are associated with greater adherence of therapists to the MST model. The association between treatment fidelity and outcomes for adolescents has been repeatedly demonstrated in trials of MST [35,39,48,50]. To mitigate the dissipating influence of poor adherence, the MST developers have developed an extensive quality assurance system [62]. In common with all MST sites, the 10 START trial sites were licensed by MST Services Inc. (Charleston, SC, USA), and therefore participated in MST Services’ quality assurance procedures. As well as the weekly supervisions with the MST supervisor, the therapists receive a one-hour weekly telephone consultation with an MST expert, on-site booster training sessions four times per year, and twice-yearly implementation reviews by the MST expert. The supervisor guides clinical work according to the MST Supervisory Manual, and in delivering MST the trial team adheres to the MST Organizational Manual [63].

